#### Health economic analysis

To assess potential welfare effects of the intervention, a cost-efficiency analysis (CEA) and a cost-utility analysis (CUA) will be conducted. Effect measures of the intervention are changes in COPM for the CUA and changes in e.g. grip strength for the CEA. Detailed registration of time spent at each home will enable us to establish the aggregate costs associated with provision of services for individuals in both groups. The hourly wage including pay roll tax and other taxes for the different categories of staff members will be applied. Costs will vary according to the duration and/or type of competence that is offered to each participant. The detailed time registration will make it possible to differentiate between types of staff with respect to costs. An incremental cost efficiency ratio (ICER) will be calculated.

Potential long-term changes in the intervention group will be examined after 15 months. Employing the panel data structure, variations in cost per unit change in effect measures across individuals will be analysed, controlling for gender, age, and other variables. Both fixed effect and random effect models will be estimated.

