**Health-care services and cost measures**		
Warranted community-based assistance in time of inclusion	*Type of assistance wanted*	t1
	Home-helper/Nurse/Auxiliary nurse/Occupational therapist/Physiotherapist/Nursing home placement long term/Nursing home placement short term/Assisted living/Meals on Wheels/Safety alarm/Rehabilitation	
Inpatient and outpatient treatment since last assessment	*Frequency and type of co-interventions*	t2, t3
	Hospital admissions/Admissions to other institutions/Day centre placement/Outpatient treatment	
Current home-based assistance offered	*Presence and frequency of home-based assistance*	t2, t3, t4
	Home-helper/Nurse/Auxiliary nurse/Occupational therapist/Physiotherapist/Meals on Wheels/Reablement/No assistance	
Current community institution-based service offered	*Type of institution-based service offered*	t4
	Nursing home placement long-term/Nursing home placement short-term/Day placement/Other institution placement/No institution placement	
Usage of home-based services	*Daily time registration in minutes of working time used during home-visits*	t5
	Home-helper/Nurse/Auxiliary nurse/Occupational therapist/Physiotherapist/Social educator/Assistant/Speech therapist/Student	

t1 = baseline assessment, t2 = 3 months after baseline assessment, t3 = 9 months after baseline assessment, t4 = 15 months after baseline assessment, t5 = daily assessment during 9 months after baseline assessment.

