#### Primary outcome

The primary outcome will be performance of activities of daily living and satisfaction with that performance, measured by the COPM
[12]. During a semi-structured interview, the participant will be encouraged to identify problems with their self-care, productivity and leisure activities. The participant will thereafter rate importance of each identified activity on a 1 to 10-point scale, before the five most important activities are rated for performance and satisfaction with performance, again on 1 to 10-point scales (higher scores reflect higher importance, better performance or higher satisfaction). A change of two points is regarded as a clinically relevant improvement or deterioration
[12].

A literature review based on 19 methodological studies
[13], concludes that COPM is a valid, reliable, clinically useful and responsive outcome measure. The Norwegian version of COPM has been tested for validity and responsiveness
[14] and reliability
[15] in persons with rheumatic diseases with good results. Psychometric properties have also been found satisfactory in elderly persons with a variety of diagnoses
[14, 16, 17].

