#### Secondary outcomes

Functional mobility will be measured using the Timed Up and Go (TUG) Test, which was developed as a short test of basic mobility skills in frail community-dwelling elderly persons
[18]. The participant will be encouraged to walk fast without compromising safety. The time taken to rise from a chair with arm rests, walk 3 m, cross a line on the floor, turn, walk back, and sit down again will be registered. Normative data for home-dwelling older adults exists
[19]. Test-retest reliability
[19] and intrarater reliability
[18] in community-dwelling elderly people has been found to be excellent and moderate, respectively. Criterion validity
[18] and construct validity
[20] has also been found to be excellent and moderate, respectively, in a community-dwelling older population.

Grip strength will be measured with the hydraulic instrument, Jamar Dynamometer. The participant will sit in front of a table holding the dynamometer. With the elbow at 90 degrees flection, the participant will be asked to grip and squeeze the dynamometer as hard as possible. Both hands will be tested twice. The mean of the two assessments will be calculated. Normative values for average grip strength in an elderly population are available
[21]. The instrument has been tested for criterion validity in a normal population
[22] and test-retest reliability in community-dwelling older adults
[23] with excellent results.

Health-related quality of life will be measured by the COOP/Wonka, which is a generic, self-reported outcome measure
[24]. The chosen revised version
[25] consists of six questions with associated drawings, where each question represents a separate domain. The responses are scored on a five-point ordinal scale ranging from 1 to 5 (1 = best, 5 = worst). In a structured review, COOP/Wonka was found to have weak evidence of reliability, adequate evidence of validity, and good evidence of responsiveness in an elderly population
[26].

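### The cost-utility analysis uses COPM, which is not a utility, and the stated costing covers only staff time in the home although the research question concerns health-care resources in general

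*Protocol article*

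**What the plan says.** The Health economic analysis section announces that "a cost-efficiency analysis (CEA) and a cost-utility analysis (CUA) will be conducted". It then assigns the outcomes: "Effect measures of the intervention are changes in COPM for the CUA and changes in e.g. grip strength for the CEA".

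The Primary outcome section describes COPM as an interview in which the participant names problem activities, after which "the five most important activities are rated for performance and satisfaction with performance, again on 1 to 10-point scales". The only generic quality-of-life measure is COOP/Wonka, which "consists of six questions with associated drawings, where each question represents a separate domain". The economic section does not use it.

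For costs, the same section says "Detailed registration of time spent at each home will enable us to establish the aggregate costs associated with provision of services for individuals", priced at the hourly wage (taxes included) of each staff category. The Outcomes section describes the cost outcomes as use of home-based services, registered daily for 9 months as minutes in the home. Table 2 gives the unit as "Daily time registration in minutes of working time used during home-visits".

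Table 2, under a heading that names cost measures, also records the frequency and type of "Hospital admissions/Admissions to other institutions/Day centre placement/Outpatient treatment" at t2 and t3 (3 and 9 months). Research question 2 asks which intervention makes the more cost-effective use of health-care resources, without limiting this to home care.

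**The concern.** Two things do not fit together.

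On the effect side, a cost-utility analysis expresses benefit in a preference-based utility, so that the ratio can be set beside those of other programmes. A ratio per COPM point does not have that property, and the label invites readers to treat it as if it did. In addition, naming the second effect measure only by example leaves the denominator of that ratio to be chosen after the data are seen.

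On the cost side, the numerator is narrower than the question. If reablement changes how often people are admitted or seen outside the home, the stated costing cannot show it. It could miss a real saving, or treat a participant whose home visits stop during an admission as cheaper. The protocol's Background reports an earlier randomised trial in which reablement was followed by fewer approvals for higher-level care, less need for emergency department treatment, and lower aggregated health and home-care costs. These are partly services that the stated costing leaves out.

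**Working it through.** The economic section states no figure, so there is none to reproduce. The check is a comparison of the protocol's own definitions, followed by an illustration under stated assumptions.

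**Effect side**

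- Required for a CUA: an outcome valued by preferences on a common scale.
- Provided (Primary outcome section): 1 to 10 ratings of performance and satisfaction on up to five activities, which differ between participants. No preference weights or anchors are described.
- Alternatives in Table 2: Timed Up and Go, grip strength and COOP/Wonka. COOP/Wonka has six separate ordinal domains, and no value set or mapping to a utility is described.
- Result: no planned measure supports the CUA label. The analysis with COPM is a cost-effectiveness analysis.

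**Cost side**

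| Item | Recorded? | Priced in the stated costing? |
|---|---|---|
| Staff minutes in the home | Daily for 9 months | Yes, at hourly wage |
| Hospital, other institution, day centre, outpatient | t2 and t3, both arms, frequency and type | No price or step given |
| Community institution placement (separate item) | t4 only, when only the intervention group is assessed | No |
| Travel; any supervision or team time outside the home | Not in the registered minutes | No |

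The cost difference left out, reablement minus control, is the sum over service types k of u_k × (N_kR − N_kC). Here u_k is the unit cost of service k, and N_kR and N_kC are the mean numbers of contacts per participant in the reablement and control arms. This sum is zero if use is equal between arms, and otherwise can take either sign. The protocol gives neither u_k nor N_k, so it cannot be evaluated.

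**Illustration for one participant (all inputs assumed)**

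Assume constant daily home care over 274 days (about 9 months), no home minutes while admitted, D admitted days, and a price per admitted day of r home-care days.

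- Home minutes only: change in cost = −D/274. For D = 7, 14, 30 and 60 this is −2.6%, −5.1%, −10.9% and −21.9%.
- With admissions priced: change in cost = (r − 1) × D/274. For D = 30 and r = 2: 1 × 30/274 = +10.9%. For D = 30 and r = 10: 9 × 30/274 = +98.5%.

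For a single participant the two methods differ in sign whenever r is above 1. This shows the mechanism only and says nothing about the difference between arms.

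**The case against.** The strongest reply is that this is a condensed article. It nowhere says that home minutes are the only cost. Service use is listed under a heading that includes cost measures, the Discussion promises service consumption and related cost data, and unit-cost tables commonly belong in a fuller plan. This stands in part: the data are gathered, and a fuller document might price them. But the article does more than stay silent. The Outcomes section describes the cost outcomes as home-based services in minutes, and the economic section builds aggregate costs from that time. That text needs correcting wherever the details sit.

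Several stronger readings are tempting but not supported:

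- *That the omission would reverse the cost comparison between arms.* This needs prices and a difference in admissions, and the protocol gives neither. The eligibility criteria also exclude people already in need of institution-based rehabilitation or a nursing home place, which makes admissions less likely without ruling them out.
- *That a planned QALY result cannot be produced.* The protocol plans no QALY and names no threshold. The fault is the label, and a ratio per COPM point remains usable under another name.
- *That reablement's overhead is excluded.* Therapist minutes and training visits in the home are registered, and where supervision takes place is not stated. Only work outside home visits is missed, and travel arises in both arms. Whether start-up training belongs in the cost is a choice of perspective.
- *That COPM performance alone should be the effect.* The protocol makes performance and satisfaction both primary.

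**Conclusion.** The point holds in two parts. First, the CUA is misnamed: this follows directly from the protocol's own description of COPM and from the absence of any utility instrument in Table 2. The other effect measure is also left open. Second, the costing as stated is narrower than research question 2 and does not use the service data recorded in both arms at 3 and 9 months. A shift of care from home to institution would therefore not be counted as a cost.

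The second part rests on taking the Outcomes and Health economic analysis sections as the costing rule. The direction and size of any bias cannot be computed from the protocol, and the percentages above depend wholly on assumed days and prices. The analysis of effectiveness is not touched. The correction should be made before the economic results are analysed, because it decides what research question 2 can be said to have answered.

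**What to change.** 1. Rename the CUA a cost-effectiveness analysis. Prespecify COPM performance and COPM satisfaction as its effects, and name any other outcomes, such as grip strength, as secondary.
2. Add the hospital, institutional, day-centre and outpatient use recorded at t2 and t3 to each participant's cost, at published unit costs per admission or contact. Table 2 lists frequency and type but not length of stay, so per-day costing would need bed-days added to the data collection.
3. If this is not done, report the result as home-care staff cost only, and draw no conclusion about overall cost-effectiveness.
4. State that travel, and any supervision or team time not spent in the home, is not captured by the registered minutes. Examine it in a sensitivity analysis over a stated range.

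The cost is a change of wording, a unit-cost table and an estimate of time outside the home. The service-use counts are already planned. The downside is some extra costing work and wider intervals for the cost difference.

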### Ethics and dissemination

The Regional Committees for Medical and Health Research Ethics (REK West, 2012/295) granted ethics approval for the study. The research will be carried out according to the Declaration of Helsinki. Personal confidentiality will be assured and a declaration of voluntary participation with information about the study purposes and consequences, emphasising the right to withdraw from the study, will be signed by each participant. The randomisation procedure is regarded as ethically acceptable, as none of the participants will receive an intervention that is below the standard she or he would otherwise have received if not participating in the trial. Besides, the control group will be offered reablement after completing 9 months follow-up. Thus, delivering an inferior rehabilitation intervention will be avoided.

We will communicate the results in peer-reviewed journals. In addition, results will be presented to health-care professionals and the public through various regional and national events and websites.

## Discussion

To our knowledge, this will be the first RCT examining the effect of reablement in a Scandinavian context. The protocol has been developed according to the SPIRIT 2013 statement
[10], follows the CONSORT statement
[11], and is registered in ClinicalTrials.gov, 2012/295. Reablement has evolved in countries like Sweden, Denmark and Norway in recent years and is increasingly being implemented in these countries. However, so far, only one Danish non-controlled study, evaluating if a home-based reablement program influenced the ability of older adults to perform activities of daily living, has been published in Scandinavia
[30]. Current evidence from international reablement is also sparse and inconclusive
[5–9] and evidence from high quality RCTs is lacking. This paper outlines the protocol for a study where the main aim is to assess the effects of reablement on a long-term basis. The trial uses a randomised controlled design, which is considered the gold standard for testing the effect of a specific intervention.

In this trial, a combination of a patient-specific measure (COPM), standardised generic measures (TUG, Jamar Dynamometer), and a questionnaire with standardised items (COOP/Wonka) will be used. The intention is that the combination of instruments will capture the multi-component nature of the experimental intervention and the effects it has on the ability to perform daily activities, functional capacity and health-related quality of life. This will also allow for comparison of populations and results across studies. In addition, the study will provide socio-demographic, health-care service consumption, and related cost data. Thus, despite the modest sample size, it will be a comprehensive study with the potential to capture a diversity of outcomes.

One limitation in the study will be the lack of blinding of participants and health-care providers. We will, however, record and evaluate the success rate of the assessor blinding strategy. Another possible limitation will be the risk of contamination from the intervention arm of the study to the control arm. Due to potential problems with recruitment in a rather sparsely inhabited municipality, the intervention will be implemented in all home-care districts in the municipality. Hence, it will not be possible to avoid the same health-care personnel providing both the experimental and control interventions, even though this will be to different participants. As a consequence, the differences between the groups may be diminished.

A third limitation may be the nature of the COPM interview, which, in a previous study, was found to have a therapeutic effect independent of further interventions
[31]. In the COPM interview and scoring process, the participants in both groups will be encouraged to verbalise important activity limitations and participation restrictions. This may have an effect that results in perceptual and behavioural changes initiated by the participant, which again may blur the effects of the reablement intervention. On the other hand, reablement is a goal-directed and individualised intervention. The use of COPM will allow each participant to choose and rate the activity limitations that he/she considers important, thereby capturing aspects of everyday life that are of direct concern to the individual. As a consequence, the “noise” related to items in standardised instruments experienced as irrelevant by participants will be reduced, which in theory will have the potential to make the COPM more responsive to capturing the effects of reablement. In addition, the described activities will be used as a basis for discussing both long-term and short-term goals for reablement, thus enhancing communication and an active role for the participant in the reablement process.

In conclusion, this study will contribute to the knowledge of the effect and cost-effectiveness of reablement in community-dwelling adults.

## Abbreviations

CEA: Cost-efficiency analysis
CONSORT: Consolidated standards of reporting trials
COPM: Canadian occupational performance measure
CUA: Cost-utility analysis
ICER: Incremental cost efficiency ratio
RCT: Randomised controlled trial
SPIRIT: Standard protocol items: recommendations for interventional trials
TUG: Timed up and go.
